### Method monitoring

#### Data monitoring

There will be no data monitoring board. The study team will comply with data collection and management procedures which has been approved by the Thailand ethics committee and abide by the rules of medical confidentiality.

#### Harms

We do not expect adverse events to occur and will not collect data on adverse events as this will create an unnecessary burden on the participants. The short break leaders will remind participants to be careful when doing the movements and ask participants to check that there are no tripping hazards before they engage in any movements.

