#### Social-level components

##### Team movement breaks

The social intervention consists of organising short group-based movement breaks, with each cluster forming a team. Each cluster will be encouraged to take four movement breaks of at least 4 min each at 9.30 am, 10.30 am, 2.30 pm and 3.30 pm, within a 60 min time window after the listed timings. An exercise or dance video with music will be played, and participants are encouraged to dance/exercise along with the video. Alarms will signal that it is time for a movement break. If participants work from home, they will be encouraged to join the breaks together online through video conferencing software such as Zoom.

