### Outcomes and measurements

#### Data collection

The duration of the research will be 18-months from the start of the intervention (6-months of intervention and 12-months follow-up, in addition to the baseline data collection), and participants will be requested to remain continuously enrolled during this period. Figure 1 provides an overview of the timeline of the PAW trial. Survey data will be collected at four time points: baseline, 6th month, 12th month and the 18th month after baseline assessment. Data will be collected by a trained research team, supervised by the core research team to ensure the quality and consistency of the data collected. The survey will be interviewer-administered. Trained physicians or nurses will take invasive cardiometabolic measurements at baseline, 6th month, and 12th month. Demographic information will only be measured at baseline. The main challenge will be to trigger sustained adherence to short breaks and not just a short-term behaviour change. In that regard, implementing a follow-up period that is sufficiently long to assess these long-term effects is essential. As a token of appreciation, all participants who have completed follow-up at 6th, 12th and 18th month will receive compensation of 500 THB (US $16) at 6th month, and 250 THB (US$ 8) each at 12th and 18th month. In total, they will be compensated 1000 THB (US $32) if they have participated until the end of the trial.

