#### Tertiary outcomes

Quality-Adjusted Life Years (QALYs) will be obtained from three surveys for cost-effective evaluation. One is the EuroQol-5 Dimension (EQ-5D-5L), where participants will be able to rate the severity of their disease [44]. The instrument encompasses five dimensions: mobility, self-care, usual activities, pain/discomfort and anxiety/depression. Participants will be asked to rate their health state on five levels of severity. QALYs will also be taken from work productivity, which will be assessed using the Work Productivity and Activity Impairment Questionnaire (WPAI) and musculoskeletal health which will be assessed using the Standardised Nordic Questionnaire [45]. In addition, the study will ask participants for demographic information and self-report of comorbidities. For candidates with pre-existing health conditions or metabolic risk factors (e.g. hypertension, diabetes, hyperlipidemia) we will collect additional data on the history of disease and medication dosage.

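### The decision not to collect adverse events leaves a six-month exercise-break trial with no event-level harms data, although interviews already scheduled in both arms could supply it

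*Protocol article*

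**What the plan says.** The Harms section gives the rule and its reason in one sentence: "We do not expect adverse events to occur and will not collect data on adverse events as this will create an unnecessary burden". It then has break leaders remind participants to take care and "ask participants to check that there are no tripping hazards before they engage in any movements". The neighbouring Data monitoring section adds: "There will be no data monitoring board". No other section of the article provides for recording adverse events.

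On exposure, Data collection describes "6-months of intervention and 12-months follow-up, in addition to the baseline data collection". Team movement breaks says "Each cluster will be encouraged to take four movement breaks of at least 4 min each" and "An exercise or dance video with music will be played, and participants are encouraged to dance/exercise along with the video". The lottery section puts the recommended number at 20 breaks a week.

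On who is exposed, the eligibility criteria exclude mobility-limiting disability, extended leave and pregnancy, but not cardiometabolic disease. Tertiary outcomes expects such participants: "For candidates with pre-existing health conditions or metabolic risk factors (e.g. hypertension, diabetes, hyperlipidemia) we will collect additional data".

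On existing contacts, surveys are scheduled at baseline and at 6, 12 and 18 months, and "The survey will be interviewer-administered". Table 1 lists WPAI, EQ-5D-5L, the Standardised Nordic Questionnaire, pre-existing diseases and health utilisation at all four times.

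**The concern.** Expecting no events is an assumption about the intervention. A trial can normally check such an assumption, but this rule removes the means of doing so. The same section also asks participants to look for tripping hazards, so it does foresee a physical risk.

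The background section says the results are to help the Thai government develop a benefit package under Universal Healthcare Coverage. Decision-makers would have estimates of benefit and cost but no count of falls, injuries or cardiac events by arm. Events not asked about during the trial cannot be recovered reliably afterwards.

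**Working it through.** **1. Each stated reason against the rest of the article.**

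- *Events are not expected.* The protocol schedules four exercise or dance breaks a day for six months, admits people with hypertension, diabetes or hyperlipidaemia, and gives a tripping precaution. It cites no event rate in support of the expectation.
- *Collection is a burden.* At each survey round participants answer an interviewer and wear an accelerometer for 10 days. They also give 15 ml of blood at baseline, 6 and 12 months. A few more questions are small beside this. The 6-month interview falls at about the end of the intervention, so it covers the exposure period.

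**2. What the planned instruments can and cannot show.**

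| Planned item | What it gives by arm | What it does not give |
|---|---|---|
| Standardised Nordic Questionnaire | musculoskeletal symptoms | whether a fall or injury occurred, and when |
| EQ-5D-5L | pain, mobility, other dimensions | cause or seriousness |
| WPAI | productivity loss | whether an event caused it |
| Health utilisation | care used | relation to a break |

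The economic evaluation counts the cost of treating musculoskeletal disease, diabetes and hypertension. Harm could therefore show indirectly and be partly costed, but not as attributable events.

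**3. Arm sizes for an illustration.** The protocol's own sample size gives these, and it reproduces.

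- Inputs: difference 23.3 min, SD 45.5, two-sided 5%, power 80%. The two-sample t-test gives 60.8, so 61 per arm.
- Design effect 1 + ((CV² + 1)m − 1) × ICC, with m = 22.1, CV = 11.6/22.1 and ICC = 0.05, is 2.36.
- 61 × 2.36 = 143.96, so 144 per arm and 288 in total. 288/0.8 = 360, or 180 per arm if split equally.

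**4. What recording would make possible.** If no events are seen among n people, the exact one-sided 95% upper bound on risk is 1 − 0.05^(1/n), or roughly 3/n.

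- n = 180: 1.65% exact; 3/180 = 1.7%.
- n = 144: 2.06% exact; 3/144 = 2.1%.
- With the protocol's design effect borrowed for a harm outcome (an assumption): 180/2.36 = 76.3 gives 3.9%, and 144/2.36 = 61.0 gives 4.8%.

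**5. Events that might be there to record.** The article gives no risk, so these six-month risks are assumed, with n = 180 and independence. Expected events are 180p. The chance of at least one is 1 − (1 − p)^180.

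| Assumed risk p | Expected events | Chance of at least one |
|---|---|---|
| 0.5% | 0.9 | 59% |
| 1% | 1.8 | 84% |
| 2% | 3.6 | 97% |
| 5% | 9.0 | >99.9% |

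Without collection, none of these risks can be told apart from zero using direct event counts.

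**The case against.** The best defence is that this is a low-intensity behavioural trial. Breaks last a few minutes, a break counts towards the lottery at 100 steps, and people with mobility-limiting disability and pregnant women are excluded. The breaks were piloted with 10 intervention participants. The ethics committee approved the data procedures, and the Harms section carries a precaution. All of this stands and lowers the urgency. None of it records an event.

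A reader might infer that harms would go wholly unseen and uncosted. The documents do not support that. Symptoms, care use, productivity and quality of life are measured in both arms, and some treatment costs are counted. The gap is event-level data.

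A reader might also infer that the trial needs a monitoring board. Nothing in the article shows that a trial of short office breaks does, and the remedy does not depend on one.

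Nor does the volume of exposure establish risk. At full adherence, 180 × 20 × 26 = 93,600 participant-breaks. At the incentive threshold of 14 a week, 180 × 14 × 26 = 65,520. Both assume an intervention arm of exactly 180 and no leave, whereas offices of 7 to 40 workers are randomised. A count of breaks says nothing about how many cause harm.

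Finally, participants are unblinded, so self-reported events may be reported unequally. That is a reason for neutral, identical questions in both arms. It does not justify asking nothing.

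**Conclusion.** The point holds in a limited form. The protocol fixes a rule under which the trial will have no event-level harms data, and the burden reason is weak given the interviews both arms already attend. The indirect measures soften the gap but do not close it.

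Its size cannot be taken from the documents, which give no event rate. The upper bounds of about 1.7% and 2.1% are illustrations that assume no events, complete follow-up of 180 or 144 people, and independence. Clustering would widen them.

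A reader might go further and conclude that injury-related dropout would bias the primary result, since withdrawal needs no reason and the primary analysis is complete-case. The article gives no evidence of such dropout. No primary estimate, test or sample size is shown to be affected. This is a cheap and worthwhile improvement to harms reporting, not a condition for the validity of the main analysis.

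**What to change.** Replace the Harms sentence with a short structured item, worded identically in both arms, at the existing 6-, 12- and 18-month interviews. It should ask about any fall, injury, cardiac event or musculoskeletal event that needed care or time off. For each event it should record the date, the care needed and what the person was doing at the time. The last question shows relation to a break without a differently worded form for controls. Report counts by arm, with the 6-month interview as the main one because it covers the intervention period; the later interviews fall after it.

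If break leaders also log events during breaks, report that log separately and descriptively for the intervention arm only. Control offices have no such breaks to log, so adding the log to the by-arm counts would ascertain events unequally.

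The cost is a few survey questions, a protocol amendment and a minute or two per interview, with some risk of asymmetric reporting because participants know their arm. The sample size and the planned analyses stay as they are. The change works best if made before the 6-month interviews.

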#### Auditing

There will be no independent audit of the trial. NHEALTH [43] and the data collectors from the MOPH will manage the security and quality according to their standard operating procedure.

#### Pilot feasibility study

We conducted a quantitative and qualitative internal pilot feasibility study with 20 convenience-sampled office workers (10 in intervention and 10 in control group) from a department, the Health Intervention and Technology Assessment (HITAP), in the MOPH. This study was conducted before the main study with two key objectives. Firstly, to assess the feasibility and acceptability of the interventions (e.g. having four short-breaks per day) and the criteria used to measure intervention adherence. Participant inclusion criteria were the same as for the main study. Two out of three offices from HITAP were chosen to take part in the study. The offices that were chosen were the furthest apart from one another to reduce the chance of spillover effects. Participants within the offices volunteered to take part in the study and were not randomly chosen. All participants wore the AcitGraph activity accelerometer to measure SB and PA. The intervention group also wore Fitbit devices to measure their step count during the short breaks. Findings from this pilot study informed iterations of the main study interventions and protocol. Secondly, this study included two interviews that were done to investigate the relevance of the interventions by understanding: (i) perceived definitions and knowledge related to SB and PA; (ii) perceptions related to SB and PA in the office including barriers and facilitators; (iii) opportunities to reduce SB and increase PA in the office; and (iv) how participants perceived the intervention and all its components. The results of the pilot study will be published separately.

#### Sample size

Eligible office workers from the DMS will be invited to participate in the trial. To detect a difference in the primary outcome of 23.3 min in sedentary time per day as reported in a prior randomised trial [22], the sample size was calculated with a standard deviation (SD) of 45.5, based on a two-tailed significance level of 5% and power of 80%. The calculation assumes a conservative intra-cluster correlation coefficient of 0.05 and a coefficient of variation of 0.52 to account for varying cluster sizes in the study. There are 18 clusters (offices), each cluster varying between 7 to 40 office workers. The mean cluster size was 22.1 with a standard deviation of 11.6. Assuming an average cluster size of 22 participants, we will yield a design effect of 2.36. Therefore, the total sample size required to detect a difference of 23.3 min in SB is 288 participants. To conform to best practice, this sample size will be inflated by 20% to account for dropouts and potential loss of participants due to non-compliance to primary outcome or chances of faulty devices. Hence, a sample size of 360 participants is needed.

### Data analyses

#### Primary and secondary outcomes

The primary aim of this study is to investigate the impact of introducing short movement breaks during office hours on SB of office workers both during and outside working hours. This primary analysis will be conducted using a linear mixed-effect model with daily time spent in SB as the dependent variable and the intervention allocation as the independent variable. The model will be adjusted for confounders such as baseline SB, baseline characteristics (such as age and gender), device wear times and stratification factor defined by office size, when necessary. The model will account for possible intra-cluster correlation of individuals within the same office.

In our primary analysis mentioned above, we will adopt the complete case analysis approach where missing values will not be replaced. Secondary and tertiary outcomes relating to PA, cardiometabolic outcomes, quality of life, and productivity will be analysed using a similar methodology. These analyses will be conducted at 6-month and 12-month follow-up to investigate the effectiveness of the intervention as well as post-intervention behavioural maintenance. Sensitivity analysis using the intention-to-treat approach where missing data will be imputed will also be carried out for the primary outcome of our study. Baseline characteristics of participants who are lost to follow up or dropped out of the study will be compared to those who completed the study to investigate differential dropout between intervention and control groups. All evaluations will be performed using a two-sided test at 5% level of significance.

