### Intervention group

#### Individual-level components

##### Fitbit

The intervention group will be given a Fitbit device (Inspire HR) to track their PA throughout the trial. The proper use of the device will be explained in a self-help program booklet. Fitbit is an activity device that uses a tri-axis accelerometer to provide real-time feedback and allows self-monitoring of steps, as well as calories burned, distance covered, active minutes, heart rate, time asleep each day and proportion of hourly activity completed amongst others [35]. It provides feedback through a smartphone app via Bluetooth connection. The device also sets haptic vibration feedback for hourly activity during office hours (9 am to 6 pm) to nudge participants to walk at least 250 steps each hour. Participants will be encouraged to wear the device as frequent as possible to obtain the most accurate results.

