#### Measurement timeline of outcomes

The primary outcome will be measured at baseline, 6th month, 12th month and 18th month follow-up. The non-invasive cardiometabolic outcomes will be measured at baseline and every 6 months until the 18th month. The invasive cardiometabolic outcomes will only be measured at baseline, 6th month and the 12th month. The tertiary outcomes such as the EQ-5D-5L, musculoskeletal health, WPAI and self-report comorbidities will be measured together with the non-invasive cardiometabolic measures at baseline, 6th, 12th and the 18th month (Table 1). The economic impact will be evaluated at 6th month and the end of the trial follow-up period.

**Table 1 Tab1:** Overview of study outcomes and measurement instruments used (docx)

	Baseline	6 months	12 months	18 months
Objectively measured sitting, upright time and step count				
10-day ActiGraph	x	x	x	x
Self-reported demographics				
- Age	x			
- Gender	x			
- Nationality	x			
- Marital status	x			
- Education	x			
- Pre-existing diseases	x	x	x	x
- Smoking and alcohol consumption	x	x	x	x
Questionnaire:				
- Work Productivity and Activity Impairment questionnaire (WPAI)	x	x	x	x
- General Physical Activity Questionnaire (GPAQ)	x	x	x	x
- EuroQol-5 Dimension (EQ-5D-5L)	x	x	x	x
- Standardised Nordic Questionnaire	x	x	x	x
- Health utilisation	x	x	x	x
Health-related outcomes				
- Body weight	x	x	x	x
- Body height	x	x	x	x
- Neck, waist, and hip circumference	x	x	x	x
- Blood pressure	x	x	x	x
Biomarkers				
- Fasting plasma glucose, HbA1c	x	x	x	
- Fasting insulin	x	x	x	
- Lipid profile: triglyceride, total cholesterol, high density lipoprotein cholesterol (HDL-C), low density lipoprotein cholesterol (LDL-C)	x	x	x	
- High sensitivity C-reactive protein (hs-CRP)	x	x	x	

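### The named outcome analyses stop at month 12, although sedentary time and the other non-blood outcomes are collected to month 18 and sustainability is a stated aim

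*Protocol article*

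**What the plan says.** All references are to the protocol article.

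- **Analysis time points** (Data analyses, Primary and secondary outcomes): "These analyses will be conducted at 6-month and 12-month follow-up to investigate the effectiveness of the intervention as well as post-intervention behavioural maintenance". Month 18 is not mentioned.
- **Collection of the primary outcome** (Measurement timeline of outcomes): "The primary outcome will be measured at baseline, 6th month, 12th month and 18th month follow-up".
- **Collection of questionnaires** (Data collection): "Survey data will be collected at four time points: baseline, 6th month, 12th month and the 18th month after baseline assessment". The tertiary outcomes "will be measured together with the non-invasive cardiometabolic measures at baseline, 6th, 12th and the 18th month". Table 1 agrees: ActiGraph, all questionnaires, anthropometry and blood pressure are marked at month 18. Only the blood biomarkers end at month 12.
- **Aim** (end of Background): aim (ii) is whether the change in behaviour is sustained.
- **Reason for the long follow-up** (Data collection): "implementing a follow-up period that is sufficiently long to assess these long-term effects is essential". The same section sets a six-month intervention followed by twelve months of follow-up.
- **Economic evaluation** (Measurement timeline of outcomes): "The economic impact will be evaluated at 6th month and the end of the trial follow-up period".
- **Device** (Fitbit): "The intervention group will be given a Fitbit device (Inspire HR) to track their PA throughout the trial".

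**The concern.** The article does not leave the analysis time points open. It names two, ties them to maintenance of behaviour, and leaves out the last one at which the primary outcome is measured. That conflicts with its own schedule, with aim (ii) and with its argument for a long follow-up.

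Two things are at stake. An effect that is present at month 12 and fades by month 18 would have no named comparison to show it. And with month 18 unnamed, whether it is reported becomes a choice that could be made after the results are known. The results are meant to inform a national benefit package, so durability matters to the intended reader.

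A smaller point of wording goes with this. If Fitbit use runs for the whole trial while the intervention is said to last six months, it is unclear whether the later comparisons are properly called post-intervention.

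**Working it through.** **1. The plan's own figure.** The sample size is checked first, to see whether it depends on the later time points.

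- Inputs (Sample size): difference 23.3 min, SD 45.5, two-sided 5%, power 80%, ICC 0.05, coefficient of variation 0.52, mean cluster size 22 (22.1 before rounding).
- Per arm, normal approximation: 2 × [45.5 × (1.960 + 0.842) / 23.3]² = 59.9, so 60. The t-based calculation gives 60.8, so 61.
- Design effect: 1 + [(CV² + 1) × m − 1] × ICC. With m = 22 and CV = 0.52 this is 2.35. With m = 22.1 and CV = 11.6/22.1 = 0.525 it is 2.36, as stated.
- Total: 2 × 61 × 2.36 = 287.9, matching 288. Then 288 / 0.8 = 360.

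The figures reproduce. The primary outcome is set at month 6, so naming month 18 changes none of them.

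**2. Collection against analysis.**

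| Outcome | Collected after baseline (months) | Outcome analysis named (months) |
|---|---|---|
| ActiGraph sedentary time and activity | 6, 12, 18 | 6, 12 |
| GPAQ, WPAI, EQ-5D-5L, Nordic | 6, 12, 18 | 6, 12 |
| Anthropometry, blood pressure | 6, 12, 18 | 6, 12 |
| Blood biomarkers | 6, 12 | 6, 12 |

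Only in the last row do collection and analysis agree.

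**3. Size of the gap.**

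- Post-intervention period: 18 − 6 = 12 months.
- Covered by the named analyses: 12 − 6 = 6 months, and 6/12 = one half.
- Follow-up ActiGraph rounds: three collected, two with a named comparison.

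**4. Which clock the labels use.** The primary outcome section speaks of follow-up at the sixth month, and the measurement timeline of follow-up at the eighteenth, both counted from baseline. On that clock, 12-month follow-up means month 12. If both labels were counted from the end of the intervention instead, 6-month follow-up would be month 12, and the analysis would skip month 6, where the primary outcome lies.

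**5. What the sentence covers.** It may refer to the secondary and tertiary outcomes alone or include the primary model. In the first case, sedentary time has no named maintenance analysis at all. In the second, it has one at month 12 only. Neither reading gives a month-18 comparison.

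**6. The economic evaluation.** It compares the arms by net benefit regression on working hours, absenteeism and presenteeism, clinical indicators such as cardiovascular risk scores, and QALYs. It is evaluated at month 6 and at the end of follow-up, so it can draw on month-18 EQ-5D-5L and WPAI data. Sedentary time and physical activity are not on its list.

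**The case against.** **The label may mean month 18.** The Data collection section divides the trial into six months of intervention and twelve of follow-up. The analysis sentence uses a similar pair of durations, for effectiveness and then maintenance, in that order. Taken phase by phase, 12-month follow-up could be the end of the follow-up phase. This is the best counter-argument, and it shows that the label is ambiguous. The baseline-counted visit labels elsewhere favour month 12, and if month 18 was meant, the same wording change settles it.

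**It could be left to an analysis plan.** That would hold if the article were silent. It names the time points, and they do not fit its own schedule.

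**The month-18 data are not idle.** This stands in part. A reader might infer that nothing at all is planned for month 18. The documents do not support that, because the economic evaluation plans between-arm estimates at the end of follow-up. The gap concerns sedentary time, physical activity and the other non-blood measures as trial outcomes.

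**Other stronger readings.**

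- A reader might infer that hourly Fitbit prompting continues to month 18 and so contaminates the later contrasts. The article ties the whole-trial wording to tracking of activity; the vibration prompts come in a separate sentence with no stated duration. What stands is that device use and intervention length need to be reconciled.
- A reader might take 288 to 360 as the number of participants whose month-18 data go unanalysed. Those figures are the requirement for the primary comparison and the recruitment target. Neither forecasts month-18 attendance, and the article itself warns of loss over a long follow-up.
- A reader might conclude that a single repeated-measures model is required. Separate baseline-adjusted mixed models at each visit are valid, so that is a preference.

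**Conclusion.** The point holds in this form: the article names months 6 and 12 for its outcome analyses and no between-arm comparison of sedentary time, physical activity or non-invasive outcomes at month 18, although those data are collected and sustainability is a stated aim. Maintenance is therefore tested 6 rather than 12 months after the six-month intervention. Stopping at month 12 is right only for the blood biomarkers.

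This rests on visit labels being counted from baseline, which is the reading most consistent with the rest of the article. The month-6 primary result, its error rate and the sample size are untouched, and month 12 still gives one test of maintenance. The point should be corrected because a stated aim is affected, but it does not threaten the main result.

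**What to change.** In Data analyses, Primary and secondary outcomes, give the time points as 6, 12 and 18 months after baseline, with 6 and 12 months for blood biomarkers, and say that sedentary time is included. Use the same baseline-adjusted linear mixed model with allowance for clustering by office. Keep month 6 as primary and label months 12 and 18 as the maintenance comparisons. A joint repeated-measures model is optional. If month 18 is deliberately left out, state why.

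Reconcile the Fitbit section with the Data collection section on whether device use continues after month 6, and name the month-12 and month-18 comparisons to match.

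The cost is a change of wording and one further model run per non-blood outcome. No new data, visits or participants are needed.

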The study is designed as a two parallel-group cluster randomised superiority trial. The primary outcome assesses sedentary time at the 6th month. The aims of the study are to evaluate (i) the impact of a multicomponent short-break office intervention on minutes spent sedentary during office hours. In addition, the study will also evaluate the effect of the intervention on secondary outcomes such as PA, cardiometabolic risk factors and productivity (ii) the sustainability of the behavioural change; and (iii) the cost-effectiveness of the short-break office intervention. The cost-effectiveness analysis will allow the results to be compared with other trials’ economic evaluations. The results of this study will assist the Thai government in developing health promotion and disease prevention benefit package under the Universal Healthcare Coverage (UHC) scheme. Filling this knowledge gap might also help inform investments on short break interventions in the private sectors.

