### Potential difficulties and limitations and alternative approaches

Identification of effect sizes might be indirect for data with repeated measures. As such, care will be taken to use alternative estimation techniques such as multilevel linear mixed-effect model and adjusted standard errors to ensure robust results from treatment effects when evaluating the impact of the interventions. We may not be able to follow people for a prolonged period due to loss to follow-up.

In conclusion, the current cluster randomised controlled trial will assess the effects of a multicomponent PAW behavioural intervention in reducing sitting time and increasing PA in desk-based office workers in the longer-term as compared to usual practice. In addition, from a company and societal perspective, we will provide insight into the cost-effectiveness of the intervention as compared to usual practice. We will also assess if a reduction in sitting time and increase in PA is related to the quality of life, health and work-related outcomes, and how the PAW intervention can be further improved.

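### The plan for the sustainability aim gives arm comparisons at 6 and 12 months but no estimate of how the arm effect changes after month 6, and it omits the 18-month data

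*Protocol article*

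**What the plan says.** The closing paragraph of the Background lists "the sustainability of the behavioural change" as the second aim. The Data collection section gives 6 months of intervention and 12 months of follow-up. It justifies the long follow-up by the need to see whether adherence lasts. The Measurement timeline section and Table 1 schedule accelerometer-measured sedentary time at baseline and at 6, 12 and 18 months.

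Under Data analyses, Primary and secondary outcomes, the model is a "linear mixed-effect model with daily time spent in SB as the dependent variable and the intervention allocation as the independent variable". It is adjusted for baseline sedentary time and other covariates as needed. On clustering, the section says: "The model will account for possible intra-cluster correlation of individuals within the same office". On missing data: "we will adopt the complete case analysis approach where missing values will not be replaced". On timing, the analyses will be "conducted at 6-month and 12-month follow-up to investigate the effectiveness of the intervention as well as post-intervention behavioural maintenance". All evaluations use a two-sided 5% test.

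Two provisions bear on attrition: a comparison of the baseline characteristics of dropouts and completers, and this: "Sensitivity analysis using the intention-to-treat approach where missing data will be imputed will also be carried out for the primary outcome of our study".

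The only other relevant text is in the section on potential difficulties and limitations. For repeated-measures data it says that "care will be taken to use alternative estimation techniques such as multilevel linear mixed-effect model and adjusted standard errors".

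**The concern.** Sustainability is a question about how the arm difference moves once the intervention stops. The article assigns that question to the arm comparison made at two visits. It names no visit term, no arm-by-visit term and no 12-minus-6-month difference. A reader of the results would therefore have two arm effects, each with its own test, and no interval for the change between them.

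One significant and one non-significant result do not show that an effect was lost. Two significant results do not show that it was fully kept. With complete cases at each visit, some of any change could also reflect who dropped out between visits.

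The 18-month measurements, which say most about lasting change, have no place in the stated maintenance analysis. The results are meant to inform a national benefit package, so it matters whether a kept effect can be told from a partly faded one.

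**Working it through.** **Inputs from the Sample size section.** Difference 23.3 min/day, SD 45.5, two-sided 5%, power 80%, ICC 0.05, coefficient of variation 0.52, mean cluster size 22.1 (SD 11.6), design effect 2.36, 18 offices, 288 participants before and 360 after allowance for dropout.

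**The plan's own figure.** An individually randomised t test needs 61 per arm. The design effect is 1 + ((CV² + 1)m − 1) × ICC. With m = 22.1 and CV = 11.6/22.1 it is 2.36. Then 61 × 2.36 = 143.96, rounded up to 144 per arm, or 288 in total, and 288/0.8 = 360. Both figures reproduce and are not in dispute.

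**Assumptions not in the documents.** 288 analysed at month 6; a further 10% lost by month 12; correlation r of 0.3 to 0.8 between the two arm-effect estimates; normally distributed estimates tested against t with 16 degrees of freedom (critical value 2.12). The design effect is either the stated 2.36 or 1.97, which the same formula gives for 288/18 = 16 analysed per office and CV 0.52.

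**Standard errors.**
- Month 6: 45.5 × √(4 × DE/288) = 7.53 min (DE 1.97) or 8.24 min (DE 2.36).
- Month 12: divided by √0.9, giving 7.93 or 8.68 min.
- Change: √(SE6² + SE12² − 2r·SE6·SE12). For DE 2.36 and r = 0.3 this is √(67.9 + 75.3 − 42.9) = 10.0 min.

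**Power at each visit if 23.3 min is fully kept.** 83.5% (DE 1.97) or 76.1% (DE 2.36) at month 6; 79.3% or 71.3% at month 12. The joint probability comes from the bivariate normal distribution. The chance of significance at month 6 only is the month-6 power minus the joint probability.

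| DE | r | SE of change (min) | Fully kept: significant at 6, not at 12 | Same, among trials positive at 6 | Halved: also positive at 12, among trials positive at 6 |
|---|---|---|---|---|---|
| 1.97 | 0.3 | 9.2 | 14.9% | 17.8% | 28.3% |
| 1.97 | 0.8 | 4.9 | 9.1% | 10.9% | 30.8% |
| 2.36 | 0.3 | 10.0 | 18.4% | 24.2% | 25.1% |
| 2.36 | 0.8 | 5.4 | 10.9% | 14.3% | 28.6% |

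**Less pessimistic inputs.** With no further loss, equal standard errors of 8.24 min, a critical value of 1.96 and r from 0 to 0.8, the first pattern still occurs in 15.5% down to 6.9% of trials.

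**Where the two tests do work.** If nothing is left at month 12, about 2% of trials positive at month 6 are also positive at month 12. If everything is kept, 76 to 89% are.

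**What a direct contrast would offer.** The 95% half-width is 2.12 × SE, about 10 to 21 min. Power to detect loss of half the effect (11.65 min) is about 17 to 60%.

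Attrition enters these figures only as lost precision. Any bias from selective dropout is not quantified.

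**The case against.** The strongest reply is that this is a journal article. The form of a longitudinal model and the definition of maintenance usually belong in an analysis plan that is not shown. That would settle the matter if the article were silent, but it says which analyses serve maintenance, and those do not estimate a change.

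The second reply is that a reader might infer two separately fitted models and a verdict reached by comparing p-values. The text says neither. Analyses at two visits is the natural reading, but the limitations section mentions multilevel models for repeated measures, so a joint model is not excluded. That section defines no contrast, however.

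A reader might also infer that the trial cannot tell a kept effect from a lost one. The documents do not support this. The 12-month comparison is randomised and separates full retention from complete loss well. The ambiguity lies in partial fading. Nor is it an error to call a halved effect persistent, because the article never says that maintenance means full retention.

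Nor would the two visits involve different people. With modest further loss the samples largely overlap, and imputation and a dropout comparison are planned. Whether the imputation reaches month 12 is unclear. The Primary outcomes section sets the primary outcome at 6 months, while the Measurement timeline uses the term for sedentary time at every visit.

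Finally, the direct contrast is itself imprecise. That is correct, and it limits what the remedy can promise.

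**Conclusion.** The point holds in a limited form. The stated analysis answers whether an effect remains at 12 months. It does not estimate how much of the 6-month effect is kept, and it leaves out the 18-month data collected for long-term follow-up. If the two visit results were read against each other, a fully kept effect would look lost in about 9 to 18% of trials. Among trials positive at 6 months, 25 to 31% would also be positive at 12 after the effect had halved. These figures rest on the assumed correlation of 0.3 to 0.8, 10% further loss and a design effect of 1.97 to 2.36. The 6-month primary comparison and its sample size are unaffected. This is a worthwhile improvement to the analysis of aim (ii), not a flaw in the trial's main result.

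**What to change.** Keep the 6-month arm difference as the primary test and keep the 12-month arm difference.

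For aim (ii), add one linear mixed model of sedentary time at 6, 12 and 18 months. Include arm, visit, arm-by-visit, baseline sedentary time and stratum, with random effects for office and participant, and use every participant with any follow-up. An office-by-visit term is worth adding if it can be estimated, because without it the standard error of the change may be too small.

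Report the arm effect at each visit, and its change from month 6 to months 12 and 18, with 95% confidence intervals. State that neither maintenance nor loss will be inferred from significance at individual visits. State also whether the imputation analysis covers the later visits.

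The cost is some wording and one extra model on data already scheduled for collection. The drawback is precision: a standard error of about 5 to 10 min for the 6-to-12-month change, against a 23.3-min effect, means it should be presented as an estimate with its interval and not as a powered test.
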